## Introduction

Anaemia is a condition in which the number of red blood cells or their oxygen carrying capacity is insufficient to meet physiological needs [1, 2]. Anaemia can be classified into three categories: severe, where haemoglobin is <7.0 g/dl; moderate, where the haemoglobin is 7.0–9.9 g/dl; and mild, where haemoglobin is 10–10.9 g/dl [3]. According to World Health Organization, anaemia is considered to be of public health significance if population studies find a prevalence of ≥5.0% [4].

Globally, about 56% of pregnant women in low- and middle-income countries have anaemia. Sub-Saharan Africa has the highest prevalence of anaemia among pregnant women (57%), followed by South East Asia (48%) and the lowest prevalence (24.1%) in South America [5, 6]. In Tanzania, the prevalence of anaemia among women (15–49 years) is 44% in Mainland and 60% in Zanzibar [7]. The prevalence of anaemia among pregnant women in some regions of Tanzania include 68% in Dar es Salaam [8] and 47.8% in Kilimanjaro [9]. In Dodoma region, there is a scarcity of recent information on the prevalence of anaemia among pregnant women, but one past study that was conducted in Dodoma reported high prevalence (63.8%) [10].

Studies have shown several factors that can cause anaemia during pregnancy; these include micronutrients deficiencies (such as iron, folic acid, vitamin A and vitamin B_12_) and parasitic diseases, such as malaria and hookworm [9, 11–14]. Although the contribution of each of these factors to anaemia during pregnancy differs significantly by geographical location, seasons and dietary practices [15], inadequate intake of diets rich in iron is reported to be the leading cause of anaemia during pregnancy [11, 12]. Iron deficiency is the cause for 75% of all anaemia cases during pregnancy [15, 16]. Infectious diseases, such as malaria, helminth infestations and human immunodeficiency virus, are also implicated with a high prevalence of anaemia in sub-Saharan Africa [17, 18].

It has been reported that anaemia during pregnancy has negative effect on maternal and child health. These include increased maternal and perinatal mortality, increased numbers of preterm births and/or low-birth weight, impaired cognitive development in children and reduced adult work productivity [6, 19, 20]. Anaemia is also associated with intrauterine growth retardation, which is a risk factor for stunting among children of <2 years [20]. Reduction of anaemia during pregnancy can contribute significantly to achieving many of the Sustainable Development Goals (SDGs) including SDG 1 (end poverty), SDG 2 (2.2 end all form of malnutrition) and SDG 3 (3.1 maternal mortality reduction and 3.2 child mortality reduction) [21].

In Tanzania, different interventions are being implemented at health facility level to reduce the burden of anaemia during pregnancy. These include anaemia screening and treatment, supplementation of iron and folic acids (FEFO) tablets, de-worming, intermittent prophylactic treatment (IPTp) for malaria with sulphadoxine pyrimethamine (SP), free provision of mosquito nets and health education during antenatal care (ANC) visits [7]. Despite the ongoing interventions to reduce the burden of anaemia among pregnant women, the prevalence of anaemia among pregnant women in this country is still high [8–10]. This could be due to the ways in which these interventions are provided which gives opportunity to pregnant women who attend for ANC services only [7]. In case the pregnant woman fails to attend ANC clinic, will miss this opportunity and those who delay in booking their ANC visit will not receive adequate services, the lack of which may predispose them to anaemia. In Tanzania, utilization of maternal healthcare services among pregnant women is still low as it has been shown that only 24% of pregnant women had their first ANC visits in the first trimester, while 73.5% of pregnant women attended ANC in the second and third trimesters of pregnancy [7, 22]. A study conducted in Dodoma region also showed that, only 30.6% of women attended the first ANC within the first trimester of pregnancy [23]. This translates to less opportunity for receiving regular scheduled check-ups and interventions for pregnant women.

Late booking for ANC may interfere with adherence to FEFO supplementation as well as IPTp for malaria and de-worming programmes, thereby increasing the risk of anaemia in pregnancy [7]. In order to make sure that the majority of pregnant women are reached by the interventional programmes, there is a need to scale up these interventions at the community level the gap that this project aims to bridge. Moreover, there are limited interventional studies in the particular area. For instance, one study was conducted in 2002, focusing only on micronutrient-fortified beverage supplementation [10]. The current study will employ a multi-interventions module involving supplementation, IPTp for malaria, de-worming and nutritional education at the community level, where the majority of pregnant women will be reached. The aim of this study is therefore to assess a community-based nutritional education intervention to reduce the burden of anaemia among pregnant women in Dodoma City. Specifically, the objectives of this study are:

to determine the effectiveness of community-based nutritional education intervention in reducing the prevalence of anaemia among pregnant women in Dodoma City;to assess the effectiveness of community-based nutritional education intervention on knowledge of anaemia (causes, signs and symptoms, effects, risk factors, prevention, dietary influences) among pregnant women in Dodoma City; andto assess the effectiveness of community-based nutritional education intervention on dietary intakes and practices in Dodoma City.

The results from this study will help programme planners and policy makers to plan for effective intervention strategies for reducing the burden of anaemia during pregnancy. The findings of this study will also serve as the baseline information for future scholars. Utilization of the knowledge obtained will enable pregnant women to play their role by improving their diet and adherence to maternal health services, thereby reducing maternal anaemia in Dodoma Region.

## Materials and methods

### Study area

The study will be conducted in peri-urban areas of Dodoma City. Dodoma City is the capital of Dodoma region and the national capital of Tanzania [24]. Administratively, the city is divided into 41 wards (26 urban wards and 15 peri-urban wards) with approximately a total population of 410 956 and annual population growth rate of 2.7% [24]. Women comprise ∼51% of the total population [7]. The city is inhabited by different ethnic groups although the indigenous ethnic groups are Gogo, Rangi and Sandawe [24]. The main economic activities in the city include businesses, seasonal agriculture that depends on unimodal rainfall and agro-pastoral activities. The main staple foods include maize, sorghum and millet [24]. Within the city, maternal healthcare services are provided in all healthcare facilities in order to prevent maternal-associated morbidities including anaemia. However, in remote areas the healthcare facilities are located faraway; therefore, outreach services are normally carried out on monthly basis in order to provide maternal healthcare services in those areas. Anaemia is one among the nutritional challenges affecting pregnant women within the region [10] and currently there are limited studies on anaemia among pregnant women in this area.

### Study design and population

The study design will be a community-based cluster randomized controlled trial with both control and interventional arms. Four hundred pregnant women at second trimester of pregnancy (gestational age from 13 weeks and above) living in peri-urban areas of Dodoma City at the time of data collection and willing to participate will be included in the study. Pregnant women with special medical conditions, such as epilepsy, sickle cell anaemia, diabetes mellitus, hypo- or hyperthyroidism, malignancy disease, hypertension, human immunodeficiency virus, ante-partum haemorrhage, renal disease and severe anaemia will be excluded from the study. ANC card and health worker will assist in identifying the eligible participants.

### Recruitment

Participants will be recruited by community health workers and local leaders from their households. Advertisement at the community meetings/gatherings, religious centres and Reproductive and Child Health clinics and public announcements methods will be used to mobilize the community about the study.

### Intervention

Previous studies have shown that the use of nutritional education intervention, FEFO supplementation in combination with appropriate IPTp of malaria and de-worming during pregnancy reduces the prevalence of anaemia [25]. This community-based nutritional intervention will consist of the following four components: nutritional education, FEFO supplementation, de-worming and provision of IPTp.

Nutritional education

Nutrition education will be delivered by a research team member using a developed education material. The education material (see Supplementary file 1) has been developed by a research team after doing an intensive literature review from previous studies [26, 27]. The developed educational material has been modified and translated to Swahili language in order to suit our environment. Each pregnant woman in the interventional group will receive nutritional education. Nutrition education consists of the followings: definition of anaemia, symptoms of anaemia, causes for anaemia, effects of anaemia, behavioural and dietary risks for developing anaemia and prevention of anaemia. Nutritional education will be delivered during all three phases of the study. The first phase will be delivered at the time of baseline study where hard copy of education material will be provided to each participant for self-learning. The second phase will be followed 1 month after the first, and the last phase will be carried out 1 month after the second phase. Hard copy of training material will be provided only during the first phase (baseline survey), but the same education material will be used to train pregnant women about nutritional education for all the three phases of the study. The nutritional education training will be provided in groups of 10–11 women. Sessions will be interactive and are expected to last for ∼45–60 min.

ii. Supplementation of FEFO tablets

All participants in the interventional and control arms will receive one tablet of FEFO (200 mg of dried Ferrous Sulphate + 0.25 mg Folic Acid) supplement once daily as per ANC national guidelines [28] during the entire course of the study period. The FEFO supplements will be given on monthly dose basis starting at the baseline survey. Nurse midwifery will dispense the monthly dose of FEFO supplements to each participant. Monitoring of adherence to FEFO supplementation will be carried out on a monthly basis during follow-up visits.

iii. Malaria prophylaxis

All participants in the interventional and control arms will receive a dose of three SP (1500 mg of Sulphadoxine + 75 mg of Pyrimethamine) tablets on monthly basis as per ANC national guidelines [28] throughout the study period. The first dose will be given as soon as the nurse midwife confirms the gestation age of ≥13 weeks. The subsequent doses will be provided on monthly basis during follow-up visits. The SP tablets will be administered through the direct observed treatment method.

iv. De-worming

All participants in the interventional and control arms will receive a single dose of anti-helminthiasis as per ANC national guidelines [28]. Five hundred milligrams of mebendazole tablet(s) will be given to each participant as soon as the nurse midwife confirms the gestation age of ≥13 weeks. Mebendazole will be administered as a stat dose through the direct observed treatment method.

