### Sample size calculation and selection

The sample size will be calculated based on the formula for a randomized control study [29].
$$n=\frac{{\left\{Z\alpha \sqrt{\left[\pi o\left(1-\pi o\right)\right]}+Z\beta \sqrt{\left[\pi 1\left(1-\pi 1\right)\right]}\right\}}^{2}}{{\left(\pi 1-\pi o\right)}^{2}}$$
where *n* is the minimum sample size, *Zα* is the standard normal deviate (1.96) at 95% confidence level for this study, *Zβ* is the standard normal deviate (0.84) with a power of demonstrating a statistically significant difference before and after the experiment between the two groups at 90%. *πo* is the proportion at pre-intervention (baseline prevalence of anaemia 50%). *π*1 is the proportion after intervention (prevalence of anaemia after intervention proportion 35%).
$$178=\frac{{\left\{1.96\sqrt{\left[0.5\left(1-0.5\right)\right]}+0.84\sqrt{\left[0.35\left(1-0.35\right)\right]}\right\}}^{2}}{{\left(0.35-0.5\right)}^{2}}$$

With the adjustment for 10% attrition, the calculated sample size will be *n* = 198 (178/0.9). Therefore, a total of 200 pregnant women from each arm (interventional and control) will be recruited for the study. The study arms will be matched in the ratio of 1:1. A list of all wards will be obtained from the administrative authority of Dodoma City. From the list, wards from peri-urban areas will be listed and assigned random numbers. Simple random sampling technique will be used to select four peri-urban wards. Two wards based on geographical area will be assigned to the interventional arm and the remaining two wards to the control arm. From each ward, community health workers and local leaders will recruit eligible participants and invite them at a recommended and agreed place to conduct the study.

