### Data processing and analysis

Data will be cleaned, edited and coded before data analysis. Statistical Package for Social Sciences version 25.0 will be used to analyse the data. Descriptive statistics will be used to generate frequency distribution, mean, standard deviation and cross tabulation to describe the characteristics of the study participants. The comparisons between interventional and control arms will be determined using independent *t*-tests and comparisons within groups (pre/post) will be estimated using paired *t*-tests. The *P* <0.05 will be considered statistically significant. Regression analysis will be conducted to determine the predictors of haemoglobin concentration.

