The need for effective intervention studies addressing anaemia is particularly relevant to rural communities, where the prevalence of anaemia is highest and the majority of people are poor and less educated. This study will focus on peri-urban areas of Dodoma City. Dodoma is one of the regions with high prevalence of anaemia during pregnancy [10]. It has been reported that anaemia was associated with maternal death in 38.6% of cases in Dodoma region from 2007 to 2011 [33].

In most developing countries, micronutrients deficiencies and parasitic infections particularly malaria and hookworm have been reported to be strongly associated with anaemia during pregnancy [9, 11–13]. Furthermore, inadequate intake of diets rich in iron is reported to cause 75% of iron deficiency anaemia during pregnancy [11, 12, 15, 16]. A major strength of this trial is that it attempts to assess the contribution of nutritional education towards reducing anaemia and also to maximize early utilization of maternal health services among the pregnant women. Proper nutrition education will improve dietary intakes while using community health worker and local leaders, many more pregnant women will be identified and initiated into ANC services. It is hoped that this approach will be effective in reducing anaemia in pregnancy, thereby reducing perinatal morbidity and mortality.

The intensive nutrition education and the teaching material that will be provided to each pregnant woman in interventional and control arm at baseline and end-line survey, respectively, are expected to bring into positive changes to dietary habits in the future. If successful, such an approach could profoundly brings into the attention of the relevant authorities on how anaemia could be controlled using both, diet-focused and supplementation-focused approaches. If effectiveness in real-life conditions is determined, all the above features of the intervention could be scaled-up nationwide, and taken into consideration to improve the outcome for other conditions in pregnancy. In order to maximize policy relevance, it is essential to understand the context of the research, the related policy making processes and to engage key stakeholders. To achieve this, we intend to engage continuously with the health authorities from local to national levels.

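### The intervention is labelled a four-component package although only nutritional education differs between arms, and the sample size uses a before-after change as the between-arm effect

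*Protocol article*

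**What the plan says.** **What the intervention is.** In the Intervention section: "This community-based nutritional intervention will consist of the following four components: nutritional education, FEFO supplementation, de-worming and provision of IPTp". The Introduction likewise presents a multi-component module and describes its purpose so: "there is a need to scale up these interventions at the community level the gap that this project aims to bridge". The Discussion adds that, if effectiveness is shown, "all the above features of the intervention could be scaled-up nationwide".

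**Who receives what.** The Intervention section allocates three components to everyone:
- Iron and folic acid (FEFO): "All participants in the interventional and control arms will receive one tablet of FEFO".
- Malaria prophylaxis (SP): "All participants in the interventional and control arms will receive a dose of three SP".
- De-worming (mebendazole): "All participants in the interventional and control arms will receive a single dose of anti-helminthiasis".

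The Abstract reserves education for the interventional arm, and the Discussion describes the other three components as standard care for all arms.

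**What is compared.** The aim and all three specific objectives in the Introduction name the nutritional education intervention. Outcome measures defines the primary and secondary outcomes as changes in the interventional arm compared with the control arm. Data processing and analysis plans independent t-tests between arms. It then adds that "comparisons within groups (pre/post) will be estimated using paired" t-tests, with P<0.05 as the single criterion.

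**What sizes the trial.** In Sample size calculation and selection, the first proportion "is the proportion at pre-intervention (baseline prevalence of anaemia 50" per cent. The second is the prevalence after the intervention, 35%. The power statement refers both to before and after the experiment and to the two groups.

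**The concern.** A trial estimates the effect of whatever differs between its arms. Here that is education added to FEFO, SP and mebendazole, all delivered in the community to both arms. Three parts of the article do not follow from that contrast.

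1. The sample size takes its effect from a change over time. Part of any such change may come from the shared treatment or from advancing gestation, and so may also occur in the control arm. The difference between arms would then be smaller than 15 percentage points.
2. The paired tests sit beside the between-arm tests with no order of priority. A significant gain within the interventional arm could be reported as if it showed that education works.
3. The Introduction and Discussion speak of the whole package and of scaling up all its features. Every arm receives the community-delivered components, so no comparison in the trial bears on them.

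At stake are the stated power and the reach of the conclusions.

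**Working it through.** **Step 1. Which component differs between arms**

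| Component | Interventional | Control |
|---|---|---|
| Nutritional education | yes | no, during follow-up |
| FEFO | yes | yes |
| SP | yes | yes |
| Mebendazole | yes | yes |

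Write S for the effect of the shared treatment on haemoglobin, G for the change with advancing gestation and E for the effect of education. Treat them as additive, with S and G the same in both arms.
- Mean change, interventional arm: S + G + E. The paired test in this arm tests this sum.
- Mean change, control arm: S + G.
- Between-arm difference in change: (S + G + E) − (S + G) = E.

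The between-arm comparison isolates education. The paired tests do not.

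**Step 2. The plan's own figure**

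Inputs from Sample size calculation and selection: 1.96, 0.84, π0 = 0.50, π1 = 0.35, 10% attrition, 200 per arm.
- The printed formula gives (1.96 × 0.5 + 0.84 × √0.2275)² / 0.15² = (0.980 + 0.401)² / 0.0225 = 84.7, not the stated 178.
- The attrition step does reproduce: 178 / 0.9 = 197.8, rounded up to 198.
- The deviate 0.84 corresponds to 80% power, whereas the text says 90%.

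The non-reproducing 178 and the power mismatch are separate matters. Neither is needed for this point. As a benchmark, the usual two-sample formula for 50% against 35% needs 170 per arm for 80% power.

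**Step 3. Power if control prevalence does not stay at 50%**

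The article gives no expected control prevalence at end-line, so the values below are assumptions. Other settings: education arm p1 = 0.35; n = 200 × 0.9 = 180 per arm; two-sided 0.05; no allowance for clustering.

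With p0 the control prevalence, p̄ = (p0 + p1)/2 and d = p0 − p1:
- A = √[2p̄(1 − p̄)]
- B = √[p0(1 − p0) + p1(1 − p1)]
- z = (d√n − 1.96A)/B, and power = Φ(z)
- n per arm for 80% power = (1.96A + 0.8416B)²/d²

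| Control | d | d√180 | A | B | z | Power | n per arm for 80% |
|---|---|---|---|---|---|---|---|
| 50% | 0.150 | 2.012 | 0.699 | 0.691 | 0.93 | 82% | 170 |
| 47.5% | 0.125 | 1.677 | 0.696 | 0.691 | 0.45 | 67% | 243 |
| 45% | 0.100 | 1.342 | 0.693 | 0.689 | −0.02 | 49% | 376 |
| 42.5% | 0.075 | 1.006 | 0.689 | 0.687 | −0.50 | 31% | 662 |
| 40% | 0.050 | 0.671 | 0.685 | 0.684 | −0.98 | 16% | 1471 |

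A fall of 5 points in the control arm, with the education arm still at 35%, takes power from 82% to 49%.

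**The case against.** The strongest reply is that the trial already asks the right question. The objectives name education, the outcomes compare arms, the independent t-tests come first, and the Discussion says the trial assesses what nutritional education contributes. This stands. A reader might infer that the plan judges effectiveness by before-after change, so that the effect of FEFO, SP and mebendazole would be credited to the intervention. The documents do not support that: shared treatment cancels in the main comparison, and nothing in the article makes a paired test decisive.

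A reader might also take the 50% for an untreated baseline that the shared treatment is bound to lower. The article never calls it untreated. The Introduction says these measures are already provided at health facilities and that prevalence remains high despite them. The Intervention section credits a reduction in anaemia to a combination that includes education, not to the three shared components alone. So a fall in control prevalence is possible but not established, and a rise would increase power. What remains is that the plan needs a control end-line value and supplies a baseline value in its place.

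Two further replies limit the point. The power figures concern a comparison of anaemia prevalence, the basis of the plan's own calculation, whereas the declared primary outcome is change in haemoglobin. The scale-up language is conditional and drives no planned test. Even so, its condition is a result that could speak only to education.

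**Conclusion.** The point holds as a should-fix. The four-component label in the Intervention section, echoed in the Introduction and Discussion, conflicts with the allocation of three components to both arms. The randomised contrast is education alone.

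The firmest consequence lies in the sample size. A before-after change stands in for a between-arm difference, and the two agree only if control prevalence stays at 50%. On the assumed range of 50% down to 40%, power for the prevalence comparison runs from about 82% to 16%. This rests on 35% in the education arm, 180 evaluable women per arm and independence within wards. The paired tests cannot separate education from shared treatment and advancing gestation. The shared treatment does not bias the main between-arm comparison.

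**What to change.** 1. In the Introduction, Intervention and Discussion, state that the randomised element is nutritional education, added to FEFO, SP and mebendazole given to both arms. This reconciles them with the Abstract, Outcome measures and the Discussion's own description of standard care.
2. In Sample size calculation and selection, define both proportions as end-line prevalence, one for the control arm under shared treatment and one for the intervention arm. Justify the control value, and restate the detectable difference or the power.
3. In Data processing and analysis, make the between-arm difference in change the only evidence of effectiveness, and label the paired tests descriptive.
4. In the Discussion, restrict the conclusion and the scale-up statement to education, since no arm lacks the community-delivered components.

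The edits are textual; allocation, primary outcome and between-arm test stay as they are. The price is narrower conclusions and a less favourable stated power. The restated calculation may show that 200 per arm is too few, so it should be done before recruitment.
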